## Appendix 19: Phone-Based Assessments

### Abstinence Status

1. Have you smoked any cigarettes in the last 24 hours? (Call 4)
2. How many cigarettes have you smoked in the last 24 hours? (Call 4)
3. Have you smoked cigarettes in the last 7 days? (Call 1,2,3, 4, 5, 6, 7, 8, 9, 10)
4. On average, how many cigarettes have you smoked per day in the 7 days week? (Call 1,2,3, 4, 5, 6, 7, 8, 9, 10)
5. Have you smoked cigarettes in the last 30 days? (Calls 7, 8, 9, 10 )
6. On average, how many cigarettes have you smoked per day over the last 30 days? (Calls 7, 8, 9, 10 )

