### **10.7.4. Subject-Rated Non-Standardized Measures to Be Collected at All Clinic Visits**

Thirty- and 7-day point prevalence are assessed in Recent Smoking (Appendix 11), as well as compliance with prescribed medications and reasons for non-compliance, if applicable.

A participant's employment status is assessed by Work Questions (Appendix 12); this measure also allows the study staff to calculate the amount of time spent during smoke breaks during the work day.

A participant's self-efficacy and motivation to stop smoking are assessed with Predictor Questions (Appendix 13).

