**Analysis of Primary Outcome:** The primary outcome measure is biochemically confirmed 30-day continuous abstinence at the 12-week post-Target Quit Day (TQD) confirmed by carbon monoxide (CO) breath testing with CO < 7ppm. The study hypothesis is that adaptive treatment arms of the study will show higher smoking abstinence at 12-weeks post-quit attempt vs. non-adaptive treatment. An intent-to-treat approach will be taken to analyze primary outcomes such that all subjects who are enrolled in the study will be included in the primary analysis of outcomes. Outcomes will be analyzed using generalized linear regression modeling using an ANOVA-based design. An alpha criterion of 0.05 (two-tailed) will be used in all comparisons. For a conservative estimation of abstinence, subjects lost to follow-up after the point of randomization will be counted as non-abstinent. Following this, however, a sensitivity analysis will be conducted to determine the impact of this assumption, using multiple imputation procedures that model smoking outcomes in terms of “missingness” and smoking at previously observed time-points.

**Secondary smoking outcomes:** Analysis of secondary smoking outcomes will include comparison of abstinence rates in Adaptive vs. Non-Adaptive groups via self-reported 7 and 30-day continuous abstinence and number of cigarettes smoked per day at 2- and 12-weeks post TQD. Secondary smoking outcomes will be assessed using intent-to-treat principles with use of multiple imputation to account for missing data.

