## Appendix 11: Recent Smoking

*The follow questions are about your recent smoking*

1. In the last 7 days, have you smoked at all - even a puff?  
1=YES  
2 = No  
0 = Don't know
2. In the last 7 days, how many cigarettes have you smoked per **day**?  
  
\_\_\_\_\_ [0-99]
3. In the last 30 days, have you smoked at all- even a puff?  
1= YES  
2 = No
4. On average, how many cigarettes have you smoked per day over the last 30 days?  
\_\_\_\_\_

**Adherence questions- These questions will be used for phone-based assessments. Medication adherence for in-person visits will be assessed via diaries, which is found in Appendix 20.**

(CTA Dialogue)

Medications that have been given to you for this study should be taken as follows

- Patch: put on in AM and wear for 24 hours unless otherwise directed
- Study pills: are each taken two times per day, in the morning and in the evening unless otherwise directed by study personnel

1. Did you choose to use the nicotine patch or varenicline?

1= Nicotine Patch

2= Varenicline

If "Nicotine Patch" selected ,go to questions 1a-1c.

If “Varenicline” selected, go to questions 2a-2c

1a) Over the last seven days, how many days have you used the nicotine patch as prescribed?

1b) Over the last seven days, how many days have you used the pills as prescribed?

1c) If answer to 1a or 1 b is less than 7 (100% adherence), please provide reason why you did not follow the directions above.

2a) Over the last seven days, how many days have you taken the varenicline pills as prescribed above?

2b) Over the last seven days, how many days have you taken the bupropion pills as prescribed above?

2c) If answer to 2a or 2b is less than 7 (100% adherence), please provide reason why you did not follow the directions above.

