### **26- and 52-Week Call Questions**

1. Since completing your last visit with us, have you used any smoking cessation medications? (Nicotine patches, gum/lozenge, inhaler, Chantix, Wellbutrin, bupropion, or Zyban) Yes    No

2. Since completing your last visit with us, have you smoked at all, even a puff? Yes    No

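### The 30-day abstinence item at visits counts even a puff, but the phone abstinence items ask only about cigarettes, so a puff-only lapse can pass by phone and fail at the visit

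*Protocol*

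**What the plan says.** **Visits.** Appendix 11 (Recent Smoking) asks "In the last 7 days, have you smoked at all - even a puff" and "In the last 30 days, have you smoked at all- even a puff". Section 10.7.4, on measures taken at every clinic visit, says "Thirty- and 7-day point prevalence are assessed in Recent Smoking (Appendix 11"). Section 6 defines the primary endpoint by CO below 7 ppm plus one self-report item on 30-day abstinence. The Appendix 11 30-day question is the only such visit item the protocol shows.

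**Phone.** The abstinence items of Appendix 19 are worded differently:
- item 1, call 4 only: "Have you smoked any cigarettes in the last 24 hours";
- item 3, all ten calls: "Have you smoked cigarettes in the last 7 days";
- item 5, calls 7 to 10: "Have you smoked cigarettes in the last 30 days".

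None has a puff clause. The 26- and 52-week calls add a separate question: "Since completing your last visit with us, have you smoked at all, even a puff".

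**Diary.** Section 6 bases the visit 7-day endpoint at weeks 2 and 12 on CO plus a seven-day diary. Section 10.7.5 and Appendix 20 show that the diary records a daily number of cigarettes and has no puff item.

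**Endpoints and timing.** Phone-reported abstinence is a secondary objective at weeks 1, 2, 6, 12, 26 and 52, without a CO check. The call table in Section 10.4 puts call 6 one day before the 2-week visit and call 8 one day before the 12-week visit.

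**The concern.** The protocol uses two thresholds for what counts as having smoked. The visit item says that a puff counts. The phone items leave the participant to decide whether a puff amounts to having smoked cigarettes. Someone whose only lapse was a puff or two can reasonably say no on the phone and yes at the visit.

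What is at stake is the meaning of the phone abstinence endpoints and whether they can be read alongside the visit results. Phone is the only planned source at weeks 1, 6, 26 and 52, so there the looser wording defines the outcome. At weeks 2 and 12 phone and visit results can disagree because of wording alone. A statistical analysis plan could not repair this later, since a puff that was never asked about leaves no record.

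**Working it through.** No arithmetic on rates applies: the documents give no frequency of puff-only smoking and no figure to reproduce. The check is a comparison of the items.

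| Source | Window | What counts | When |
|---|---|---|---|
| Appendix 11, item 1 | 7 days | any smoking, a puff included | visits |
| Appendix 11, item 3 | 30 days | any smoking, a puff included | visits |
| Appendix 20 diary | 7 days | number of cigarettes | before visits |
| Appendix 19, item 1 | 24 hours | cigarettes | call 4 |
| Appendix 19, item 3 | 7 days | cigarettes | calls 1 to 10 |
| Appendix 19, item 5 | 30 days | cigarettes | calls 7 to 10 |
| Appendix 19, added item | since last visit | any smoking, a puff included | calls 9 and 10 |

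**Week 12.** Call 8 comes one day before the visit. If each window ends on the day of contact, the two 30-day windows share 30 - 1 = 29 days and the two 7-day windows share 7 - 1 = 6 days. Take a single puff five days before the visit, which is four days before the call. It lies inside the 7- and 30-day windows of both contacts. On the phone, items 3 and 5 can both be answered no. At the visit, both Appendix 11 items must be answered yes. The participant is then abstinent by phone and, on the primary endpoint's self-report, a smoker.

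**Weeks 26 and 52.** Section 6 sets the phone outcome here over the last 30 days. If the 12-week visit was the last one attended, the added question reaches back 26 - 12 = 14 weeks (98 days) or 52 - 12 = 40 weeks (280 days). A no covers the 30-day window. A yes cannot be placed inside or outside it. The item therefore settles only some of the cases.

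**Weeks 1 to 12.** Calls 5 to 8 have no puff item.

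**Visit 7-day endpoint.** Section 10.7.4 points to Appendix 11, where a puff counts. Section 6 points to the diary, which counts cigarettes. On the first reading the 7-day phone and visit items differ as the 30-day items do. On the second they are both cigarette-worded and the contrast largely disappears. The protocol does not say which governs.

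**24 hours.** Appendix 11 has no 24-hour item, so phone item 1 contradicts no visit question.

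**The case against.** The best reply is that little follows from the wording. A puff on a cigarette may well be reported as having smoked cigarettes, and the documents cannot settle how participants would answer. Both arms hear the same questions. Phone and visit rates would differ in any case, because only the visit has a CO check. The visit 7-day endpoint, read from Section 6, is cigarette-worded like the phone item. At weeks 26 and 52 a puff-only lapse is not invisible. All of this stands and keeps the point small. It does not remove the different wording of the two 30-day items put to the same person a day apart.

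Three stronger readings are tempting, and the documents do not support them.

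- *That the visit definition covers anything smoked, so that cigar or hookah use passes by phone and fails at the visit.* Appendix 11 names no product, and its 30-day count question asks about cigarettes. Exclusion 4 in Section 9.2 screens out users of other smoked products at entry. Later use is possible, but the difference in definition would be an inference.
- *That the phone wording feeds the sensitivity analysis of the primary endpoint.* Section 13.4 (Statistical Hypothesis, Model, and Method of Analysis) speaks of "using multiple imputation procedures that model smoking outcomes in terms of" missingness and smoking at earlier observed times. It does not say that phone data enter.
- *That the loss can be computed by moving an assumed share of non-abstinent participants to abstinent at the planned 39.7% and 23.4%.* The share has no source in the protocol. Those rates belong to the CO-confirmed primary endpoint. Under the plan the non-abstinent group also includes participants lost to follow-up, who give no phone answer that wording could change.

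**Conclusion.** The inconsistency is real and minor. The 30-day visit item counts a puff; the 7- and 30-day phone items do not say so. The contradiction is firm for the 30-day items at call 8 and the 12-week visit. For the 7-day items it depends on a source that the protocol leaves unresolved between Section 6 and Section 10.7.4. The effect is confined to the secondary phone endpoints and their comparability with visit results. Its size cannot be derived from the documents, and no direction of bias between arms is shown. The primary endpoint and its power do not depend on the phone items.

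The conclusion rests on two assumptions: that the Appendix 11 30-day question is the single item meant in Section 6, and that at least some participants would not report a puff as having smoked cigarettes.

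**What to change.** 1. In Appendix 19, reword items 3 and 5 with the Appendix 11 phrasing (as in "In the last 7 days, have you smoked at all - even a puff"), keeping the 7- and 30-day windows. Reword item 1 in the same way for consistency, keeping its 24-hour window. Leave the cigarettes-per-day items unchanged.
2. Reconcile Section 6 with Section 10.7.4 by stating which item defines the visit 7-day endpoint. If the diary is kept, add an instruction that even a puff is to be recorded. Without this step, changing the phone script would only move the inconsistency, because the phone 7-day item would become stricter than the diary.
3. If calls have already been made, record the script version for each call so that answers to the two wordings can be told apart.

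The cost is a phone-script and REDCap label edit, a clarifying sentence in the protocol and, if the diary is kept, one line on the form.

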### Medications and Side Effects

1. Are you experiencing any side effects from the medications? Yes      No
2. If yes, what side effect(s) are you experiencing?

Abnormal Dreams  
Constipation  
Rash  
Dry Mouth

Dizziness/Lightheadedness  
Headache  
Insomnia  
Nausea  
Seizures

Anxiety  
Agitation/Anger  
Vomiting  
Gas  
Other (Please describe)

3. How severe?

- |         |            |
|---------|------------|
| 1. Mild | 6.         |
| 2.      | 7.         |
| 3.      | 8.         |
| 4.      | 9.         |
| 5.      | 10. Severe |

4. When did it start?
5. How long did it last (in days)?
6. Did you stop medication?

If **more than one side effect** reported, repeat questions 3-6.

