#### 7.1.4. Concomitant Medications/Therapies

Participants enrolled in the study will continue on the medications that they are taking at the time they start the study. They will be asked not to take additional tobacco use treatment medications during the study. If they start new medications during the study, they will be asked to report this to the CTA.

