### **10.7.6. Subject-Rated Measures to Be Collected through Phone Assessment**

Participants will be followed up with by phone to answer questions about the following:

- Abstinence status
- Average number of cpd over the past 24 hours, 7 days, and 30 days
- Medications they are taking and side effects they are experiencing, if any
- Stress level
- Experience of urges
- Confidence in their ability to become tobacco free

These questions are also listed in Appendix 19

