## **11 SAFETY MONITORING AND REPORTING**

The PI is responsible for the identification and documentation of adverse events and serious adverse events, as defined below. At each study visit, the PI or designee must assess, through non-suggestive inquiries of the subject or evaluation of study assessments, whether an AE or SAE has occurred.

The DCI Safety Surveillance is responsible for tracking and reporting SAEs to external and internal monitors. The DCI Safety Team will also manage any external safety reporting required by NIH and Pfizer. The contact for this is [name], [contact].

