### **11.1 Adverse Events**

An adverse event (AE) is any untoward medical occurrence in a subject receiving study therapy and which does not necessarily have a causal relationship with this treatment. For this protocol, the definition of AE also includes worsening of any pre-existing medical condition. An AE can therefore be any unfavorable and unintended or worsening sign (including an abnormal laboratory finding), symptom, or disease temporally associated with the use of study therapy, whether or not related to use of the study therapy. Abnormal laboratory findings without clinical significance (based on the PI's judgment)

should not be recorded as AEs. But laboratory value changes that require therapy or adjustment in prior therapy are considered adverse events.

From the time the subject signs the informed consent form through the End of Study visit (as defined in Section 10.3), all AEs must be recorded in the subject medical record and adverse events case report form. The investigator will follow all reportable events until resolution, a return to baseline condition or stabilization.

AEs will be assessed according to the CTCAE version 4.0. If CTCAE grading does not exist for an AE, the severity of the AE will be graded as mild (1), moderate (2), severe (3), life-threatening (4), or fatal (5).

Attribution of AEs will be indicated as follows:

- Definite: The AE is clearly related to the study therapy
- Probably: The AE is likely related to the study therapy
- Possible: The AE may be related to the study therapy
- Unlikely: The AE is doubtfully related to the study therapy
- Unrelated: The AE is clearly NOT related to the study therapy

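### The phone form used at ten of the fourteen scheduled adverse-event contacts does not ask about adverse events as the protocol defines them

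*Protocol*

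**What the plan says.** Section 11.1 defines an adverse event without regard to cause. It covers anything unfavourable "temporally associated with the use of study therapy, whether or not related to use of the study therapy", and it includes a pre-existing condition that gets worse. All such events are to be recorded from consent to a visit called End of Study. Attribution is a separate step on a five-level scale.

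The Schedule of Activities in Section 10 marks adverse-event assessment at the Enrollment, Medication Response, 2-week and 12-week visits, at Calls 1 to 9 and at the 52-week call. A footnote mentions an Adverse Events questionnaire given at Enrollment to establish baseline symptoms. It is not reproduced in the appendices. For visits, Section 11 requires the investigator or a designee to establish, "through non-suggestive inquiries of the subject or evaluation of study assessments, whether an AE or SAE has occurred".

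For the calls, Section 10.7.6 lists "Medications they are taking and side effects they are experiencing, if any" and refers to Appendix 19. There, the Medications and Side Effects block begins "Are you experiencing any side effects from the medications". Item 2 is conditional on a Yes, and the severity, onset, duration and stopping items follow from it. The extra items for the 26- and 52-week calls ask only about cessation medication and smoking.

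**The concern.** The calls are scheduled to assess adverse events, but their opening question is narrower than the definition in two ways.

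- **Cause.** It asks about effects of the medications. Under Section 7.1.5 the participant does not know which medications are active, yet has to judge cause before anything is written down. An injury, an infection or a worsening chronic condition would properly be answered No.
- **Time.** It asks about the present. Something that began and ended since the last contact would also properly be answered No, and the onset and duration items would never be reached.

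Attribution is hard in this setting. Appendix 19 lists anxiety and agitation or anger among side effects, and its next block gives irritability and agitation as examples of withdrawal. A participant who blames quitting answers No to the safety question and contributes only a withdrawal score.

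At stake is the completeness of the safety record, above all once visits have ended. Side effects queried at visits and calls are also a feasibility endpoint in Section 6, so the filter bears on a reported result. The primary abstinence outcome is not affected.

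**Working it through.** The plan gives no figure for this point. The check sets the texts side by side and then lays out the contact timetable.

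**1. Definition against phone question**

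| Feature | Section 11.1 | Appendix 19, item 1 |
|---|---|---|
| Cause | Related or not | Only effects of the medications |
| Who judges cause | A separate five-level attribution | The blinded participant, beforehand |
| Time covered | Continuous from consent | The moment of the call |
| Pre-existing conditions | Worsening counts | Reached only if blamed on the drug |

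The open category for other symptoms and the past-tense duration item would widen the form, but both lie behind the Yes.

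**2. Contacts, in nominal days from the target quit day** (Schedule of Activities; phone timetable in Section 10.4)

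- Visits: −28, −14, +14, +84 (4 contacts).
- Calls 1 to 10: −27, −15, −1, +1, +7, +13, +42, +83, +182, +364 (10 contacts).
- Calls as a share of adverse-event contacts: 10 of 4 + 10 = 14.
- Calls within one day of a visit: Call 1 (−27, −28), Call 2 (−15, −14), Call 6 (+13, +14) and Call 8 (+83, +84), so 4. The other 6 stand apart: Calls 3, 4, 5 and 7 during treatment, and Calls 9 and 10 after it.

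**3. Up to week 12**

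Gaps between visits are 14, 28 and 70 days. They sum to 112 days, the 16 treatment weeks. The visit inquiry therefore spans the whole treatment period, with a longest recall of 70/7 = 10 weeks (week 2 to week 12).

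**4. After week 12**

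- Week 12 to week 52 is 40 weeks. Enrollment (week −4) to week 52 is 56 weeks. The share covered by calls alone is 40/56 = 71%.
- Study drug stops at day +84. Section 11.2.1 makes deaths, life-threatening events and unexpected events reportable for a further 30 days, to day 84 + 30 = +114.
- The next scheduled contact is Call 9 at day +182, which is 182 − 114 = 68 days after that window closes and 14 weeks after the drug stopped.
- Example: a life-threatening illness with hospital admission in week 14 (day +98) falls inside the window. If the participant has recovered by week 26, no scheduled question asks about it.

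**5. Recording window**

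Section 11.1 ends recording at an End of Study visit and cites Section 10.3. Section 10.3 is End of Treatment, at week 12. End of Study is Section 10.5, after the 52-week call. The Schedule of Activities marks adverse-event assessment at the later calls too. The document therefore does not settle whether adverse events are due after week 12.

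**The case against.** The strongest reply is that the phone form is not the only route. Section 11 requires an open inquiry at every visit, the Adverse Events questionnaire exists, Section 11.4 brings admissions for other causes into reporting, and participants may telephone with problems (Section 7.1.2). Four of the ten calls fall within a day of a visit. All of this stands, and several stronger readings that a reader might infer therefore fail.

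- **That adverse events are not collected at all.** The visit inquiry contradicts this up to week 12. The questionnaire is not reproduced, so whether it is also used at calls cannot be checked.
- **That most short events are lost.** The gaps between contacts over the 112 treatment days are 1, 12, 1, 13, 2, 6, 6, 1, 28, 41 and 1. With uniform onset, a 7-day symptom is present at some contact for 46/112 = 41% of onsets, and a 3-day symptom for 24/112 = 21%. The complements, 59% and 79%, are not estimates of loss. They assume the phone wording is used at visits as well, where Section 11 prescribes something else, and uniform onset has no support in the document.
- **That the severity scale is a contradiction.** Section 11.1 says "AEs will be assessed according to the CTCAE version 4.0". A participant's own 1-to-10 rating can stand beside a clinician's grade.
- **That medicines go unasked.** Appendix 11 covers study-drug use by phone, and Section 7.1.4 says of participants, "If they start new medications during the study, they will be asked to report this to the CTA". What is missing is only an explicit prompt for new medicines at treatment-period calls.
- **That a comparison between arms is biased.** No formal comparison of side effects by arm is specified, and a side-effect question suits a feasibility endpoint.

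None of this makes item 1 fit the purpose that the Schedule of Activities gives the calls. After week 12 there is no visit to compensate.

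**Conclusion.** The mismatch is real and worth correcting. As printed, the phone form does not elicit adverse events as Section 11.1 defines them. Up to week 12 the consequence is moderate: visits provide a second route, at the price of up to 10 weeks' recall. After week 12 it is more serious, because two calls are the only scheduled contacts for 40 weeks, and the first of them is also the first scheduled contact after the 30-day reporting window.

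This rests on three assumptions: that staff use the form as printed, that the unreproduced questionnaire is not also given at calls, and, for the period after week 12, that adverse events are still due then. The 30-day window in Section 11.2.1 shows that some events are due for part of that period under either reading of the end date. The number of missed events cannot be estimated from the document.

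**What to change.** 1. Reword item 1 of the Medications and Side Effects block in Appendix 19 so that it is neutral on cause and covers the time since the last contact. For example: Since we last spoke, have you had any new or worsening symptom, illness, injury, emergency visit or hospital stay, whatever the cause?
2. Use it at every call at which adverse events are due. Leave attribution and CTCAE grading to the study clinician. The 1-to-10 participant rating may stay.
3. Reconcile the Schedule of Activities, Section 10.7.6, Section 11.1 and Appendix 19. Include whether recording ends at End of Treatment (Section 10.3, as cited) or End of Study (Section 10.5), and state whether the Adverse Events questionnaire is used at calls.
4. Optionally, add a prompt for new medicines since the last contact, to match Sections 7.1.4 and 10.7.6.

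The cost is a revision of one form and its data fields, with no extra calls or visits. More minor, unrelated events will be recorded and will need clinician attribution.
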